#### Ethical arrangements

Trained nurse researchers approached and interviewed participants in order to ensure informed consent was obtained from study participants. The research team has considerable expertise with appropriately considering ethical issues in studies with similar methodology previously.^79 80^ We followed standard procedures for obtaining informed consent. Participants received information on local alcohol services and national advice telephone lines in the participant information leaflet.

### Component 2: survey of alcohol-related behaviours in sexual health services

Young adults and high-risk alcohol users are under-represented in national surveys. SHCs were selected as the setting for data collection to provide adequate inclusion of deprived groups and young people. Understanding how MUP might change alcohol misuse patterns in this group and/or increase use of other substances is considered a priority by policymakers. SHCs provide a convenience-sampling frame to monitor changes in behaviour within a high-risk population that includes adequate representation of both deprivation and young age. This component contributes to RA1 and RA2, specifically to investigate, among a population at high-risk of alcohol and drug-related problems:changes in alcohol misuse,how sources of alcohol consumption have changed following MUP,whether MUP has impacted on the use of psychoactive substances apart from alcohol,whether any unintended impacts of MUP, such as changes to alcohol sources and psychoactive substance use differ across age group, gender, highest educational attainment and employment status,whether any observed intervention effects vary at the second and third time points.

#### Study design

A repeated cross-sectional survey of patients attending SHCs was conducted to determine changes in drinking patterns and psychoactive substance use within this population. All patients attending three SHCs in Scotland and three in North England were invited to self-complete a short questionnaire. Data collection took place over 3 weeks at baseline and 8 and 12 months post-baseline. Timing was similar to the ED audit.

#### Study population

Patients of any age attending sexual health services participating in the study during data collection periods were approached. Patients who are unable to understand English well enough to complete the questionnaire (with assistance), or who left the clinic before an approach was made, and those deemed inappropriate by clinical staff to approach were excluded from the study.

#### Data collection

The questionnaire was offered to attendees at reception by a trained reception staff. Participants completed the questionnaire while waiting to be seen and returned it into a confidential returns box. The trained staff were available to offer assistance where needed. The confidential and voluntary nature of the study was emphasised. Similar patient completed questionnaires have been carried out as part of NHS Board work within NHS Lothian and NHS Greater Glasgow and Clyde achieving response rates of between 50% and 70% (without the assistance of support staff).

Questions covered where alcohol was procured, other substances used, the FAST tool (allowing quantification of alcohol misuse and binge drinkers) and basic characteristics (age band, sex, highest educational level). The questionnaire was designed to allow completion within between 2 and 5 min.

#### Socioeconomic position and inequalities

Trained reception staff assisted self-completion if required where literacy problems or visual impairment otherwise precluded participation. Analysis will be undertaken by highest education level, age and sex to determine if behavioural response to MUP in terms of drinking, source of alcohol and displacement is differentially patterned.

#### Outcome measures

The primary outcome from component 2, which aims to reveal unintended effects, will be the proportion of patients self-reporting psychoactive substance use other than alcohol in the last month. Secondary outcomes will be drug-specific rates of use within the last month, sources of alcohol purchase (including cross-border, internet, smuggled or moonshine), rates of higher risk drinking (as measured by FAST score>3), self-reported binge-drinking and analyses for differential displacement of use of illicit psychoactive drugs (including age, gender, highest achieved education, problematic drinkers)

#### Power calculation

We envisaged being able to recruit at least 50% of attendees at sexual health clinics at the six sites (three Scotland, three England), therefore resulting in a total of slightly over 10 000 recruits over two 3 week periods (an average of 288 per clinic per week). This would give us power of more than 80% to detect a change of ±4% from an estimated 30% in the proportion of people using drugs.

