**Methods and analysis:**

Component 1 sampled an estimated 2800 interviewees at a baseline and each of two follow-ups from four Emergency Departments in Scotland and Northern England. Research nurses administered a standardised survey to assess alcohol consumption and the proportion of attendances that were alcohol-related.

Component 2 covered six Sexual Health Clinics with similar timings and country allocation. A self-completion survey gathered information on potential unintended effects of MUP on alcohol source and drug use.

Using a natural experiment design and repeated cross-sectional audit, difference between Scotland (intervention) and North England (control) will be tested for outcomes using regression adjusting for differences at baseline. Differential impacts by age, gender and socioeconomic position will be investigated.

Component 3 used focus groups with young people and heavy drinkers and interviews with stakeholders before and after MUP implementation. The focus groups will allow exploration of attitudes, experiences and behaviours and the potential mechanisms by which impacts arise. The interviews will help characterise the implementation process.

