#### Statistical analysis

Similar analyses to the ED component will be undertaken based on regression models with site included as a fixed effect, and the proportion taking illicit psychoactive drugs as the dependent variable for the primary outcome. We will examine whether any displacement effects are sustained between six and 12 months post implementation. We will investigate interactions with defined important covariates (including age, gender, highest achieved education, problematic drinkers) to investigate the possibility of differential intervention harms.

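### Component 2 power: more than 80% for ±4 points fits a two-group comparison; the planned baseline-adjusted Scotland v England contrast has about 60% at the stated recruitment

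*Protocol article*

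**What the plan says.** The Component 2 power section (Protocol article) expects at least half of attendees at three Scottish and three English clinics to take part, "therefore resulting in a total of slightly over 10 000 recruits over two 3 week periods (an average of 288 per clinic per week"). From this it claims, for drug use: "This would give us power of more than 80% to detect a change of ±4% from an estimated 30% in the proportion of people using". It names neither the contrast nor the significance level.

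The analysis is described elsewhere. The abstract's methods paragraph says that "difference between Scotland (intervention) and North England (control) will be tested for outcomes using regression adjusting for differences at baseline". The Component 2 statistical analysis section adds: "Similar analyses to the ED component will be undertaken based on regression models with site included as a fixed effect". The ED (Component 1) statistical analysis section, to which this refers, compares intervention with control and adjusts for baseline levels.

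The Component 2 study design section describes a repeated cross-sectional survey with a baseline and two follow-ups. Its ethics section says that no identifiable personal data were collected, so respondents cannot be paired across waves.

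**The concern.** The stated power and the stated analysis do not belong to the same comparison. Each clinic lies wholly in one country, so site fixed effects absorb the overall Scotland-England difference. The effect of minimum unit pricing (MUP) can then be estimated only as the change in Scotland minus the change in England. All four country-by-period groups add sampling variance, about twice that of a two-group comparison. No within-person correlation is available to win it back, because the waves contain different, anonymous people.

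The outcome concerned is the component's primary one: use of psychoactive substances other than alcohol, chosen to detect an unintended effect of the policy. If power is overstated, a non-significant result could be given more weight as evidence against displacement than the sample supports. This power statement has its own outcome, sample and effect size, so correcting the ED power statement would not correct it.

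**Working it through.** **Inputs**
- Recruitment (Component 2, power section): 288 per clinic per week, six clinics (three per country), 3 weeks, two periods.
- Base rate 30%, change ±4, read as percentage points (same section). Read as a relative 4% (30% to 31.2%), even a two-group test would have only about 15% power.
- Significance level: not given for Component 2. I assume 5%, as in the ED power section, and two-sided, in line with the ± sign.
- Further assumptions: equal clinic sizes, 30% in both countries at baseline, England unchanged, no site-by-period variation.

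**Group size**

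288 × 6 × 3 × 2 = 10,368; 10,368 / 4 = 2,592 per country-by-period cell.

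**Reproducing the stated power**

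Two-proportion test, 2,592 v 2,592 (Scotland before v after, or Scotland v England after):
- 30% v 34%: 87.0%
- 30% v 26%: 89.4%

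Both exceed 80%. For exactly 80%, 2,134 or 1,977 per group would do.

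**Power of the planned contrast**

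SE = √{[3 × 0.30 × 0.70 + p(1 − p)] / 2,592}; power = Φ(0.04/SE − 1.96).
- Rise, p = 0.34: SE = √[(0.63 + 0.2244)/2,592] = 0.0182; power 59.6%.
- Fall, p = 0.26: SE = √[(0.63 + 0.1924)/2,592] = 0.0178; power 61.2%.

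With exactly 10,000 respondents the figures are 58.1% and 59.7%. On the log-odds scale they are 58% (rise) and 63% (fall), confirmed by 200,000 simulations (58.0% and 62.9%).

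**Detectable change and size needed**

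Change detectable with 80% power = 2.80 × SE = 5.0 to 5.1 points. For 80% power at 4 points, 4,035 (fall) to 4,192 (rise) per cell are needed, or about 16,100 to 16,800 over two periods.

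**Both follow-ups pooled, same weekly recruitment**

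SE = √{[2 × 0.21 + (0.21 + p(1 − p))/2] / 2,592} = 0.0157 (rise) or 0.0155 (fall). Power is 72% or 73%; the 80% detectable change is 4.3 to 4.4 points.

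**Higher response**

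If 288 per clinic per week corresponds to 50% response, the cells scale by 1.2 at 60% and by 1.4 at 70%:

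| Response | Cell size | One follow-up | Both pooled |
|---|---|---|---|
| 50% | 2,592 | 60-61% | 72-73% |
| 60% | 3,110 | 68-69% | 80-81% |
| 70% | 3,629 | 74-76% | 86% |

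**The case against.** The strongest reply is that recruitment of half the attendees is a planning minimum. The Component 2 data collection section reports 50% to 70% response in similar questionnaires run without support staff, whereas staff help was available here. There are also two follow-ups. At 60% response or better with both pooled, power reaches about 80% or more. This stands, and it means that the 60% figure must not be presented as a best case, even though site-by-period variation would pull it down. It does not rescue the statement as written, which rests on two periods and slightly over 10,000 recruits.

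A one-sided test does not rescue it either: two periods give 71-73%. At the stated recruitment, only a one-sided test combined with pooling passes 80% (82-83%), and the protocol states neither for this calculation.

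It is also fair to say that the section's own arithmetic is sound. The recruitment total is right and a two-group test does give more than 80%. The fault is a mismatch between the power statement and the analysis.

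A reader might go further and infer that a null result would wrongly reassure policymakers. The document does not support that: it nowhere says that non-significance will be taken as absence of displacement, and a reported confidence interval would show the imprecision. Nor does it support a rule that the upper confidence limit must exclude 4 points. Four points is a planning effect here, and the protocol gives it no status as a margin.

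**Conclusion.** The concern holds as a mismatch between stated power and planned analysis. At the stated recruitment, the contrast to be tested has about 60% power for ±4 points, and 80% power only at about ±5 points. A true 4-point rise could be missed about 4 times in 10, where the protocol implies fewer than 2 in 10. Pooling both follow-ups narrows the gap at that recruitment (72-73%) but does not close it.

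The exact percentages depend on the assumptions listed in the working. The doubling of variance does not: it follows from site fixed effects, clinics nested in countries and independent cross-sections. Actual recruitment above the minimum would raise power; site-by-period variation would lower it.

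**What to change.** Restate the Component 2 power for the country-by-period contrast, with the significance level and assumptions given:
- Baseline plus one follow-up, about 10,400 recruits: about 60% power for ±4 points; 80% at about ±5 points.
- Both follow-ups pooled at the same weekly recruitment: about 72-73% for ±4 points; 80% at about ±4.4 points.
- Label these as figures at the minimum planned recruitment. If 288 per clinic per week means 50% response, 60-70% response would give about 68-76% with one follow-up and about 80-86% with both pooled.

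Add one sentence saying that a non-significant displacement result will be interpreted from the difference-in-differences and its 95% confidence interval. No fixed exclusion margin is needed.

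The cost is wording and a less favourable stated power. The research questions section says that data collection is complete and analysis has yet to start, so no further respondents are involved and the correction can precede the results.

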#### Statistical analysis

Similar analyses to the ED component will be undertaken based on regression models with site included as a fixed effect, and the proportion taking illicit psychoactive drugs as the dependent variable for the primary outcome. We will examine whether any displacement effects are sustained between six and 12 months post implementation. We will investigate interactions with defined important covariates (including age, gender, highest achieved education, problematic drinkers) to investigate the possibility of differential intervention harms.

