## Introduction

Minimum unit pricing (MUP) of alcohol is a novel public health policy that aims to reduce alcohol-related harms across the population. In May 2012, Scotland became the first country to pass legislation to introduce MUP without reference to beverage type, a politically high profile measure,^1–3^ although some Canadian provinces have introduced beverage-specific MUP, as further described below. This paper describes the protocol for three associated studies that collect primary data to evaluate the impact of the policy in Scotland. After delays following legal challenges,^4 5^ MUP legislation was implemented in May 2018 but it is due to cease in 6 years unless shown to be effective, under a ‘sunset clause’. These studies are a key part of the evaluation planned by NHS Health Scotland, which will report to Scottish Ministers and the Scottish Parliament. The evaluation includes analyses by others of routinely collected administrative data.^6^

The overall aim of the study is to investigate the impacts of MUP on acute and chronic health harms (including by deprivation and gender and age subgroups). The study will also determine the extent to which specific unintended consequences occur. The evidence will be a key input to the decision whether the policy will continue.

Alcohol consumption is a major determinant of population health globally,^7^ and the level of alcohol-related harm in Scotland is high compared with the rest of Western Europe.^8^ Alcohol is associated with over 200 medical conditions including an increased risk of liver disease, heart disease, unintended pregnancy, sexually transmitted infections, some cancers and some injuries.^9–14^ Its impact extends beyond the individual, with adverse effects on families, communities and the wider economy.^15 16^ Furthermore, alcohol is known to be a major contributor to socioeconomic inequalities in health in the UK and elsewhere.^17–20^ From a public health perspective, alcohol therefore has considerable potential as a modifiable risk factor to be addressed to help reduce health inequalities.^21–23^

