#### Statistical analysis

We will test for differences in the outcomes between the intervention and control groups using a regression model with ED included as a fixed effect, and with individuals nested within the ED of their attendance, before and after adjustment for relevant covariates including baseline levels of alcohol-related attendance, age, gender, deprivation quintile and disease diagnostic categories. We will also attempt to determine the nature of the effect more precisely in terms of whether there is a dose-response effect according to the time since MUP was implemented (through a test of the significance of an interaction between time and intervention). We will test for interactions of the intervention with defined important covariates (including baseline levels of alcohol-related attendance, age, gender, deprivation quintile and disease diagnostic categories) to investigate the possibility of differential intervention effects and will subsequently stratify the analyses if indicated.

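### Component 2's stated power of more than 80% for a 4-point change in drug use fits a simple two-group comparison; the planned baseline-adjusted Scotland–England contrast has about 60% (one follow-up) or 72% (both pooled)

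*Protocol article*

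**What the plan says.** The outcome is a possible harm. In Component 2, the section on outcomes puts it this way: "The primary outcome from component 2, which aims to reveal unintended effects, will be the proportion of patients self-reporting psychoactive substance use other than alcohol", with last-month recall. The Introduction says of the whole project: "The study will also determine the extent to which specific unintended consequences occur".

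The power claim is in Component 2, Power calculation. The planned size is "a total of slightly over 10 000 recruits over two 3 week periods (an average of 288 per clinic per week"), across six clinics, three in each country. From this the protocol claims more than 80% power "to detect a change of ±4% from an estimated 30% in the proportion of people using drugs".

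The analysis is carried over from Component 1. Component 2, Statistical analysis: "Similar analyses to the ED component will be undertaken based on regression models with site included as a fixed effect". The Component 1 text it refers to reads: "We will test for differences in the outcomes between the intervention and control groups using a regression model", with adjustment for covariates that include baseline levels. The Abstract (Methods and analysis) describes the test as Scotland against North England with adjustment for baseline differences. Component 2, Study design, gives three waves: baseline, then 8 and 12 months after baseline.

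**The concern.** The power statement and the analysis describe different comparisons. Different people are surveyed at each wave, and every clinic lies in one country only. Once each clinic has its own fixed effect, a country main effect cannot be estimated. What remains is how far the change over time in Scotland differs from the change over time in North England. That contrast uses four independent proportions, so its variance is about twice that of a comparison of two proportions of the same size. A power figure worked out for two groups will therefore be too high.

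The direction of the outcome makes this matter more. If a benefit is missed through low power, the conclusion errs on the cautious side. If a harm is missed, the error favours the policy. A reader who sees a non-significant result next to a claim of more than 80% power may give it more weight as reassurance than the data carry, and the results feed into the decision on renewing the policy.

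**Working it through.** **Inputs.** From Component 2, Power calculation: 288 recruits per clinic per week, 3 weeks per wave, three clinics per country, base rate 30%, change of 4 percentage points either way. Assumptions: two-sided 5% level (Component 2 gives none; Component 1 uses 95% significance, and the ± sign points to two sides), equal clinic sizes, independent respondents and, at first, no site-by-wave variation.

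**1. Planned size.** Per country per wave: 288 × 3 × 3 = 2,592. Two countries and two waves: 4 × 2,592 = 10,368, which agrees with the stated total.

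**2. Reproducing the stated power.** Two groups of 2,592:
- 30% v 34%: SE = √[(0.21 + 0.2244)/2,592] = 1.29 points; power = Φ(4/1.29 − 1.96) ≈ 87%.
- 30% v 26%: power ≈ 89%.

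The statement of more than 80% is reproduced as a comparison of one country with the other at one wave, or of before with after in one country.

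**3. Planned contrast, baseline plus one follow-up.** (Scotland after − before) − (England after − before), four cells of 2,592:
- Rise to 34% in one cell: SE = √[(3 × 0.21 + 0.2244)/2,592] = 1.82 points; power = Φ(4/1.82 − 1.96) ≈ 60%.
- Fall to 26%: SE = 1.78 points; power ≈ 61%.
- On the logit scale, power for the rise is about 58%.
- Detectable change at 80% power: (1.96 + 0.84) × √(4 × 0.21/2,592) = 2.80 × 1.80 = 5.0 points.
- For 80% power at a 4-point rise: about 4,191 per cell, or about 16,765 over two waves, against 10,368 planned.

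**4. Planned contrast, both follow-ups pooled.** The after cells double to 5,184:
- Rise of 4 points: SE = √[2 × 0.21/2,592 + (0.21 + 0.2244)/5,184] = 1.57 points; power ≈ 72%. Fall: about 73%.
- Detectable change at 80% power: 2.80 × √(3 × 0.21/2,592) = 2.80 × 1.56 = 4.4 points.

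**5. Site-by-wave variation (illustration only).** The protocol gives no figure. Suppose each clinic's true prevalence varies by wave with an SD of 1 point.
- One follow-up: the variance of the contrast rises by 4 × 0.01²/3, and power falls to about 46%.
- Both pooled: it rises by 2 × 0.01²/3 + 2 × 0.01²/6, and power falls to about 58%.

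**6. What a non-significant result could still contain.** With one follow-up the 95% interval has a half-width of about 1.96 × 1.80 = 3.5 points. An estimate just short of significance would have an upper limit of about 2 × 3.5 = 7 points.

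**The case against.** Four points can fairly be made for the protocol.

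First, three waves were collected, so the 60% figure need not describe the final analysis. This stands as a qualification. The power paragraph is itself based on two periods, so 60% is the right check of that sentence. The article does not fix whether the follow-ups are pooled. Pooled power, at about 72%, is still below the stated figure.

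Second, a reader might infer that substance use will be judged by a significance test alone, with non-significance taken to mean no displacement. The documents do not support that. Regression yields an estimate and an interval, and rules for reporting intervals and reading null results may be in an analysis plan that is not shown. Nowhere does the protocol say that a non-significant result will count as absence of displacement.

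Third, a reader might take 4 points as the protocol's own limit of tolerable harm. It is not presented as one: the text calls it "a change of ±4% from an estimated 30"%, a two-sided detectable change. Component 1 says that its 5% decrease would matter for public health; Component 2 makes no such statement about its 4%.

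Fourth, the article condenses a longer protocol. That may excuse missing detail, but not a power figure the article prints itself and that does not fit the analysis it describes.

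**Conclusion.** The power statement is wrong as written for the planned analysis. More than 80% holds for a two-group comparison (87–89%). For the country-by-period contrast, power for a 4-point rise is about 60% with one follow-up wave and about 72% with both pooled; the changes detectable with 80% power are 5.0 and 4.4 points. A true 4-point rise would thus be missed about 40% or 28% of the time.

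These figures rest on the planned recruitment, a 30% base rate, a two-sided 5% test, independent respondents and no site-by-wave variation. Relaxing the last assumption lowers power further. The conclusion concerns the stated power and how a null result would look beside it. It is not a finding that the study will misreport displacement, nor that it lacks a required margin. Whether to set an exclusion limit, and whether to make the pooled follow-up effect primary, are matters on which reasonable statisticians may differ.

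**What to change.** In Component 2, Power calculation, restate the power or the detectable change for the country-by-period contrast: about 60% for 4 points, or 5.0 points at 80% power, with one follow-up; about 72%, or 4.4 points, with both pooled. Say that these figures ignore site-by-wave variation.

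In Component 2, Statistical analysis, name the country-by-period estimate for substance use, with its 95% confidence interval, as the primary result. A non-significant finding should be read against that interval and not against the stated power.

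A formal limit for excluding displacement is optional. It would need the sponsor's own justification and should not simply reuse the 4 points.

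The cost is a change of wording and a less favourable stated power. The article says that data collection is complete and that analysis has yet to begin, so the change can precede the results. No new data are needed.
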